**Figure 1 figure1:**
[figure not shown]
The study implementation flowchart. BP: blood pressure; WHO PEN: World Health Organization Package of Essential Noncommunicable Disease Interventions.

**Table 1 table1:** Summary of the quantitative data collection tools and outcome measures in the third phase.

Tool/instrument	Purpose/domain	Administration time points^a^
Sociodemographic and Health Questionnaire	Background characteristics	T_0_
Anthropometry and Clinical Tests	Physical and biochemical outcomes	T_0_, T_1_, T_2_, T_3_, T_4_
Knowledge, Attitude, and Practice Questionnaire	Knowledge, attitude, practice	T_0_, T_2_
Global Physical Activity Questionnaire	Physical activity	T_0_, T_1_, T_2_, T_3_, T_4_
24-hr Dietary Recall	Dietary habits	T_0_, T_1_, T_2_, T_3_, T_4_
Alcohol Use Disorders Identification Test	Alcohol use	T_0_, T_1_, T_2_, T_3_, T_4_
Perceived Stress Scale-10 items	Perceived stress	T_0_, T_1_, T_2_, T_3_, T_4_
Pittsburgh Sleep Quality Index	Sleep quality	T_0_, T_1_, T_2_, T_3_, T_4_
Summary of Diabetes Self-Care Activities	Diabetes self-care	T_0_, T_1_, T_2_, T_3_, T_4_
Medication Compliance Questionnaire	Medication adherence	T_0_, T_1_, T_2_, T_3_, T_4_
System Usability Scale	Usability of the digital platform	T_0_, T_1_, T_2_, T_3_, T_4_
Laboratory tests	Physical and biochemical outcomes (HbA_1c_, fasting sugar, lipid profile)	T_0_, T_2_, T_4_

^a^T_0_: baseline; T_1_: third month; T_2_: sixth month; T_3_: ninth month; T_4_: twelfth month.

### Data Collection Tools

#### Qualitative Tools

##### In-Depth Interviews

In-depth interviews will be conducted with participants from community settings and community health workers to explore their experiences, perceptions, and the barriers or facilitators related to the digital interventions and the WHO PEN program.

##### Focus Group Discussions

Focus group discussions will be conducted with community members at each site to understand their collective perspectives on NCD prevention and digital engagement.

#### Quantitative Data Collection Tools

##### Sociodemographic Characteristics

Information was recorded on age, gender, marital status, educational qualification, occupation, and monthly household income (INR).

##### Anthropometric and Clinical Assessments

Data on anthropometric measurements (height, weight, and waist circumference) will be taken. In addition, blood pressure levels will be recorded using a digital sphygmomanometer, and random blood glucose levels will be recorded using a glucometer. Additionally, the third phase of the study will include laboratory tests for fasting blood sugar and lipid profiles at baseline and follow-up at 3 months, 6 months, 9 months, and 12 months.

##### Familiarity With the Use of Technology

Data will be gathered on the usage of mobile phones and the ability of the participants to read and send text messages, along with access to the internet.

##### NCD-Related Knowledge, Attitude, and Practices

This will be assessed using a series of questions about individuals' existing disease-related knowledge and their attitudes and practices toward its self-management.

##### 24-Hour Dietary Recall

A 24-hour dietary recall will be conducted to ascertain the dietary intake of the enrolled participants. The nutrient consumption within the last 24 hours will be computed for macronutrients and micronutrients, that is, energy, proteins, carbohydrates, total fiber, fat, total saturated fatty acids, total monounsaturated fatty acids, total polyunsaturated fatty acids, retinol, and vitamin E [14].

##### Physical Activity

This will be assessed using the Global Physical Activity Questionnaire. MET-minutes (metabolic equivalent of task) are calculated using the formula: Total MET-minutes=(minutes per day × MET value) × days per week [15].

##### Perceived Stress Scale

The Perceived Stress Scale is the most widely used psychological instrument originally developed for measuring perceived stress [16]. It is a measure of the degree to which situations are appraised as stressful. The Perceived Stress Scale is a 10-item test that rates the frequency of stress-related experiences on a 5-point scale from 0 (never) to 4 (very often).

##### Pittsburgh Sleep Quality Index

The Pittsburgh Sleep Quality Index is a standardized self-rated questionnaire to assess sleep quality and disturbances over a 1-month time interval [17].

##### Medication Compliance Questionnaire

Medication adherence will be assessed using a Medication Compliance Questionnaire that consists of 7 questions. A 4-point Likert scale will be used for rating each question (1=all the time, 2=most of the time, 3=sometimes, 4=none of the time), with higher scores indicating better adherence [18].

##### Summary of Diabetes Self-Care Activities

This tool will be used to examine adherence to diet, exercise, medication, and glucose monitoring among participants with diabetes [19].

##### Alcohol Use Disorders Identification Test

This tool will be used to assess alcohol consumption, drinking behaviors, and alcohol-related problems among the participants. It is a 10-item screening tool developed by the WHO that helps to identify individuals with hazardous or harmful patterns of alcohol use in both clinical and community settings [20].

##### System Usability Scale

The System Usability Scale will be used to assess the usability of the developed digital intervention. The System Usability Scale, a widely accepted 10-item tool, measures the usability of any given system or product [21].

### Data Analysis Plan

Interviews and focus groups will be audio-recorded, transcribed verbatim, and translated to English where necessary. A thematic analysis approach will be applied using NVivo software (Lumivero). Triangulation across all the data sources will enhance validity. Data will be analyzed using SPSS (version 29; IBM Corp) and R software (R Foundation for Statistical Computing). Heuristic evaluation will involve the estimation of severity ratings, frequency of usability issues, time taken to complete tasks, and interrater reliability. Descriptive statistics will include means (SDs), medians (IQRs), and proportions to summarize baseline characteristics. Between interventions and control arms, the analysis would be performed by ANCOVA or generalized linear models, adjusting for baseline values, cluster effects, and site-level covariates. Statistical significance will be set at *P*<.05, with 95% CIs.

A generalized linear mixed-effects model will be used to conduct the primary analysis, because the data are clustered and longitudinal in nature. The generalized linear mixed-effects model will include random intercepts for the clusters of communities and the individual study participants to account for the intracluster correlation and repeated measurements over time. Intervention arm, time, and their interaction will be modelled as fixed effects, with study site included as a fixed effect to control for contextual differences. To control the baseline imbalance in outcome variable values, the baseline value will be used as a covariate in the analysis. The maximum likelihood estimation within the mixed-effects framework will handle the missing data in the study, with sensitivity analyses using multiple imputation. Pairwise comparisons among the 3 study arms will be conducted. This will be adjusted for multiple testing using the Holm-Bonferroni method, with statistical significance assessed at 2-tailed α level of .05.

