## Methods

### Study Design and Setting

This is a multi-site, quasi-experimental study, using a cluster-design sampling strategy. This study adopts a mixed methods approach to assess the efficacy of using the WHO PEN in comparison with a control group that received no intervention and a digital intervention platform. The study is being conducted in urban poor settings in India across 4 sites with differing geographic and sociocultural characteristics. Allocation to study arms will occur at the community (cluster) level. Within each site, community clusters (wards/slum clusters) will be assigned to one of the 3 intervention arms to reduce contamination between participants and to align with local service delivery structures. All eligible individuals within a cluster are enrolled into the arm designated for that cluster.

The study will span 3 years and execute 3 distinct phases to achieve the 3 stated objectives. The interventions will be deployed in the third phase of the study and will include follow-up evaluations at 3 months, 6 months, 9 months, and 12 months post intervention.

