The sample size was determined to detect differences in primary outcomes (health-seeking behavior and NCD self-management) between the 3 arms. The initial sample size was adjusted for the cluster design, considering Cohen *d* as 0.30 for a small to moderate effect size, with 80% power and a significance level of 5%. Each study site will include 16 community clusters, resulting in a total of 64 clusters across the 4 sites. From each cluster, nearly 30 participants will be included with intracluster correlation coefficient of 0.02 and design effect of 1.58. The sample size will be adjusted for 15%-20% of attrition rate during the 12 months of follow-up period, resulting in the total sample size of 2400 (600 per site).

The comparative evaluation across these 3 groups will reveal differential effects on health-seeking behavior, self-management practices, and clinical outcomes. Figure 1 illustrates the study design framework, detailing the phases of data collection and intervention implementation. The summary of the quantitative data collection tools and outcome measures in the third phase of the study are described in Table 1.

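### The primary mixed model handles repeated measures through random intercepts alone, so if correlation decays over time its standard errors are too small for month-12 and early-to-late arm contrasts

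*Protocol article*

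**What the plan says.** The Data Analysis Plan names a generalized linear mixed-effects model as the primary analysis, with "random intercepts for the clusters of communities and the individual study participants to account for the intracluster correlation and repeated measurements over time". It adds that "Intervention arm, time, and their interaction will be modelled as fixed effects", with site as a further fixed effect, and that "the baseline value will be used as a covariate in the analysis". The three arms are compared pairwise with a Holm-Bonferroni correction at a "2-tailed α level of .05".

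Study Design and Setting allocates arms by community cluster and schedules "follow-up evaluations at 3 months, 6 months, 9 months, and 12 months post intervention". In Table 1 most instruments are repeated at all four follow-ups (T1-T4). Laboratory tests have two (T2, T4), and the knowledge-attitude-practice questionnaire has one (T2).

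The protocol does not say whether time is categorical or linear, names no primary time point, and gives no figure for correlation over time. It mentions no random slope, cluster-by-visit effect, serial residual correlation or robust standard error.

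**The concern.** One random intercept per cluster and one per person, with independent residuals, fix three things: constant within-person correlation at every lag, constant within-cluster correlation at every lag, and equal residual variance at every visit. Health behaviour measured over a year may well not behave like that.

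Two features of this design make it matter.

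- Baseline is a covariate. If correlation decays, baseline predicts month 12 less well than month 3, so the adjusted variance grows over follow-up. The model reports an average variance, which is too small for the last visit.
- Arms are assigned by cluster. Any drift of cluster means between visits enters the arm-by-time and month-12 contrasts directly, and a constant cluster intercept leaves it out of their variance.

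At stake are confidence intervals that are too narrow and a false-positive rate above 5% for those contrasts. The Holm procedure cannot repair this, because it works on p-values that are already too small.

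**Working it through.** **Inputs from the protocol** (Data Collection and Sampling Strategy; Data Analysis Plan): 64 clusters in all, 16 at each site; 15-20% attrition; total 2400; two-sided 5%; baseline as covariate. On cluster size and ICC it says: "From each cluster, nearly 30 participants will be included with intracluster correlation coefficient of 0.02 and design effect of 1.58".

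**Assumptions, not in the protocol:** continuous outcome with total variance 1 (person 0.98, cluster 0.02); 64/3 = 21.33 clusters per arm; T1-T4 modelled; time categorical unless a slope is named; one baseline coefficient b, equal to the mean within-person correlation of baseline with the follow-up visits; person correlation AR(1) with ρ per 3-month visit; cluster effect either constant or decaying per visit.

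**Step 1, the plan's own figures.** Design effect = 1 + (30 − 1) × 0.02 = 1.58. Total = 64 × 30 / 0.80 = 2400. Both reproduce, so 30 is the number per cluster after 20% attrition and is used below.

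**Step 2, worked case: ρ = 0.8, constant cluster effect.**

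- b = (0.8 + 0.64 + 0.512 + 0.4096)/4 = 0.5904.
- True variance of a cluster mean at T4 after adjustment: person part 0.98 × (1 + b² − 2b × 0.4096)/30 = 0.98 × 0.8649/30 = 0.02825; cluster part 0.02 × (1 − b)² = 0.00336. Sum 0.03161. SE of an arm difference = √(2 × 0.03161/21.33) = 0.0544 SD.
- Mean correlation over the six pairs of follow-up visits: (3 × 0.8 + 2 × 0.64 + 0.512)/6 = 0.6987. The random-intercept fit therefore sets residual variance at 0.98 × (1 − 0.6987) = 0.2953.
- Model variance at T4 = variance of the visit average + ¾ × residual variance/30. The 16 entries of the follow-up correlation matrix average 12.384/16 = 0.774, so the first term is 0.98 × (0.774 − b²)/30 + 0.00336 = 0.01725. The second is 0.00738. Sum 0.02464, SE = 0.0481 SD.
- Ratio 0.0481/0.0544 = 0.883. True error = 2Φ(−1.96 × 0.883) = 8.4%. At the first Holm step (5%/3 = 1.67%, z = 2.394) it is 2Φ(−2.394 × 0.883) = 3.5%.
- T4 minus T1: baseline and the constant cluster effect cancel. Ratio = √[(1 − 0.6987)/(1 − 0.512)] = 0.786; error 12.4%.

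**Step 3, add cluster decay of 0.8 per visit.**

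- Month 12, true: (0.98/30 + 0.02) × 0.8649 = 0.04555, SE 0.0653.
- Month 12, model: 0.05267 × 0.4254 + ¾ × 0.3013/30 = 0.02994, SE 0.0530. Ratio 0.811, error 11.2% (5.2% at the first Holm step).
- T4 minus T1: true 2 × 0.488 × 0.05267 = 0.0514; model 2 × 0.3013/30 = 0.0201. Ratio 0.625, error 22.0%.

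**Step 4, range** (model SE / true SE, then true error at nominal 5%).

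| Person correlation | Cluster effect | Month 12 | T4 − T1 | Linear arm-by-time slope |
|---|---|---|---|---|
| AR(1) 0.5 | constant | 0.97, 5.7% | 0.86, 9.2% | 0.81, 11.3% |
| AR(1) 0.8 | constant | 0.88, 8.4% | 0.79, 12.4% | 0.74, 14.9% |
| AR(1) 0.95 | constant | 0.815, 11.0% | 0.755, 13.9% | 0.71, 16.5% |
| constant 0.6 | decay 0.8 | 0.88, 8.5% | 0.76, 13.5% | 0.74, 14.6% |
| AR(1) 0.8 | decay 0.8 | 0.81, 11.2% | 0.63, 22.0% | 0.59, 25.1% |
| constant 0.6 | constant | 1.00, 5.0% | 1.00, 5.0% | 1.00, 5.0% |

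A simulation of 4,000 trials per setting with 21 clusters per arm gave 8.0%, 12.2% and 14.5% for the second row, and 11.5%, 22.1% and 25.2% for the fifth.

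**Step 5, where it does not bite.** The time-averaged arm effect has ratio 1.00 in every setting. T4 minus T3 with a constant cluster effect has a standard error that is too large (ratio 1.14 to 1.28, error 1.2-2.6%). The knowledge-attitude-practice score has one follow-up, so no lag structure arises.

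**Step 6, laboratory tests at T2 and T4, ρ = 0.8.** Here b = (0.64 + 0.4096)/2 = 0.5248.

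- Constant cluster effect, month 12: true variance 0.98 × 0.8455/30 + 0.02 × (1 − b)² = 0.0321; model 0.98 × (0.82 − b²)/30 + 0.0045 + ½ × 0.98 × 0.36/30 = 0.0282. Ratio 0.937, error 6.6%. T4 minus T2 is correct.
- Cluster decay 0.8: month-12 error is 8.4%.

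**The case against.** The strongest objection is that this is a condensed article. It says the model will include these intercepts, not that nothing else will be included, and residual covariance is often left to the analysis plan. That stands as far as it goes: a reader might infer that the plan excludes serial correlation or robust standard errors, and it does not. But the article does not leave the subject open. It names the intercepts as the means of dealing with repeated measurements, and that stated choice implies constant correlation.

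Several stronger readings are tempting and are not supported.

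- That standard errors are too small whenever correlation decays, or for every arm-by-time contrast. Step 5 shows the time-averaged effect is correct and adjacent-visit interactions can be conservative.
- That five visits are modelled and a month-12-versus-baseline interaction is tested. With baseline as a covariate, the natural reading has at most four outcome visits, and that interaction is not in the model.
- That the trial's headline comparison is invalid. No primary time point or time coding is given. If the pairwise comparisons are averages over follow-up, they are not affected.
- That the percentages are estimates for this trial. They rest on assumed decay.

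One might also argue that with two laboratory follow-ups only cluster decay could matter. That holds for T4 minus T2 but not for the month-12 difference, where the baseline covariate still produces unequal variances (6.6% in Step 6). Finally, the article also mentions ANCOVA; a single-visit ANCOVA would avoid the problem, but the mixed model is the analysis named as primary.

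**Conclusion.** The point holds conditionally. As written, the primary model assumes constant correlation over follow-up. If correlation decays, its standard errors are about 3-18% too small at month 12 and 14-25% too small for T4 minus T1 with a constant cluster effect; they are 19% and 37% too small if person and cluster correlation both decay at 0.8 per visit. The corresponding true errors at nominal 5% are about 6-11% and 9-14%, and then 11% and 22%.

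These figures use the protocol's ICC and cluster size, but the decay rates, a continuous outcome, an equal split of clusters and a common baseline slope are assumptions. With constant correlation the error is 5%. The matter is type I error and interval coverage, not power: for d = 0.30, even the larger month-12 SE gives 0.30/0.0653 = 4.6 standard errors. The change should be made, but the point does not invalidate the design.

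**What to change.** First, state whether time is categorical or linear, and which arm contrast is primary (month 12, average over follow-up, or change between visits).

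For continuous outcomes, keep the random cluster intercept, add a random cluster-by-visit effect, and replace the person intercept with an unstructured or heterogeneous autoregressive within-person covariance over the follow-up visits. Fit by REML with Satterthwaite or Kenward-Roger degrees of freedom.

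For binary, count or other non-Gaussian outcomes, where that recipe does not carry over directly, use cluster-robust standard errors clustered on community with a small-sample correction. Use the same fallback if the continuous model does not converge, which is plausible because the cluster-by-visit variance would be small at an ICC of 0.02.

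The cost is analysis wording, slightly wider intervals and a more complex fit. Visits, sample size and data collection are unchanged.

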### Strengths and Potential Limitations

A mixed methods approach will be utilized, integrating insights from behavioral, clinical, and qualitative measures to capture multidimensional outcomes. The human-centered design will ensure the digital intervention is tailored to the context of the target population, enhancing relevance and user engagement. The inclusion of geographically and culturally diverse sites such as Delhi (plains), Dehradun (valley), Chennai (coastal), and Sikkim (hilly) would provide an additional contextual understanding that would support external validity. Moreover, the incorporation of digital monitoring systems facilitates real-time data acquisition and guarantees the integrity of the interventions.

However, this study anticipates certain limitations. The nonrandomized allocation of participants may introduce selection bias, although cluster-based assignment and analytical adjustments will be employed to minimize its effects. Additionally, variations in digital literacy among participants may influence engagement with the intervention. Despite these constraints, the study is expected to yield robust insights into the differential effectiveness, user experience, and implementation feasibility of digital solutions for NCD prevention within the low- and middle-income country-setting contexts.

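### The primary model lets the arm effect vary by visit but gives the baseline covariate one slope, so a baseline imbalance could leak into the arm-by-time terms if that slope changes over follow-up (minor)

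*Protocol article*

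**What the plan says.** The Data Analysis Plan of the protocol article sets out the primary model in some detail. It says "A generalized linear mixed-effects model will be used to conduct the primary analysis, because the data are clustered and longitudinal in nature". The random part is "random intercepts for the clusters of communities and the individual study participants". The fixed part is given as "Intervention arm, time, and their interaction will be modelled as fixed effects", and site is added as a further fixed effect. Baseline then enters with the sentence "To control the baseline imbalance in outcome variable values, the baseline value will be used as a covariate in the analysis". Arm-by-time is the only interaction named.

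Study Design and Setting plans "follow-up evaluations at 3 months, 6 months, 9 months, and 12 months post intervention". Table 1 schedules most instruments at all four follow-ups, laboratory tests at months 6 and 12, and the Knowledge, Attitude, and Practice (KAP) questionnaire at month 6 only. Strengths and Potential Limitations concedes that "The nonrandomized allocation of participants may introduce selection bias" and relies on cluster assignment and analytical adjustment to limit it.

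**The concern.** The baseline value does not change over a participant's follow-up visits. Entered as a plain covariate, it gets one slope, roughly the average of the slopes that each visit would have on its own. If the link between baseline and follow-up weakens with time, that slope adjusts too little at early visits and too much at late ones. Arm is allowed to interact with time and baseline is not, so any leftover that differs between arms is taken up by the arm-by-time terms.

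In a randomised trial the expected imbalance is zero and this hardly matters. Here allocation is not randomised, and the covariate is in the model precisely to deal with imbalance. With no intervention effect at all, an arm that starts higher on the outcome could show a small apparent gain at month 3 that has reversed by month 12, and this could be read as an effect that fades. The problem would exist even if baseline were measured without error and were the only confounder.

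**Working it through.** **Inputs from the article (Data Collection and Sampling Strategy).** 64 clusters, about 30 participants per cluster, intracluster correlation 0.02, design effect 1.58, attrition 15%-20%, total 2400, planned effect d = 0.30. These figures agree with one another: 1 + (30 - 1) x 0.02 = 1.58; 64 x 30 = 1920; 1920 / 0.80 = 2400. They set the scale of the simulation below and do not otherwise bear on the point.

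**Inputs that are assumed, because the article gives none.** A baseline imbalance of 0.1, 0.2 or 0.3 SD in one arm, and three patterns of baseline-to-follow-up slope over months 3, 6, 9 and 12:

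- constant: 0.50 throughout
- mild fading: 0.60, 0.55, 0.50, 0.45
- strong fading: 0.70, 0.60, 0.50, 0.40

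**Formula.** For a linear model with complete data and random intercepts, the common slope is the mean of the visit slopes. Under no intervention effect,

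bias at visit t = (slope at t - mean slope) x imbalance.

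The change from month 3 to month 12 has bias (slope at 12 - slope at 3) x imbalance. A term that is constant over visits cancels from a within-participant difference, so with complete data a single baseline slope gives this contrast no adjustment at all.

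**Strong fading.** The mean slope is (0.70 + 0.60 + 0.50 + 0.40) / 4 = 0.55.

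- At 0.2 SD: month 3, (0.70 - 0.55) x 0.2 = +0.03 SD; month 12, (0.40 - 0.55) x 0.2 = -0.03 SD; difference -0.06 SD.
- At 0.3 SD: +0.045 and -0.045 SD; difference -0.09 SD. The single-visit figure is 0.045 / 0.30 = 15% of the planned d.

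**Mild fading.** The mean slope is 0.525. At 0.3 SD, month 12 has (0.45 - 0.525) x 0.3 = about -0.023 SD; the difference from month 3 is -0.045 SD.

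**Constant slopes.** Zero at every visit. In all three patterns the deviations from the mean slope sum to zero, so an arm contrast averaged equally over the four visits has no bias.

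**Null simulation.** 64 clusters (21, 21 and 22 per arm) of 30, intracluster correlation 0.02, four follow-ups, random intercepts, no intervention effect, 1,000 runs per setting. The table gives the rejection rate of the joint arm-by-time test at nominal 5% with one common baseline slope:

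| Slope pattern | 0.1 SD | 0.2 SD | 0.3 SD |
|---|---|---|---|
| Constant 0.50 | 4.6% | 4.9% | 6.0% |
| Mild, 0.60 to 0.45 | 5.9% | 6.9% | 10.6% |
| Strong, 0.70 to 0.40 | 9.5% | 19.0% | 36.6% |

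With a separate baseline slope at each visit, the rate was 4.5%-5.9% in all nine settings, and the month-12-minus-month-3 contrast was within 0.003 SD of zero. Simulation error at a true 5% is sqrt(0.05 x 0.95 / 1000) = 0.7 percentage points (one standard error). With no imbalance, the common-slope model rejected 5.3%-5.7% of the time.

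**Incomplete data.** Maximum-likelihood mixed-model fits with cluster and participant intercepts (64 clusters of 37, 18% dropout, strong fading, 0.2 SD imbalance) gave a month-12-minus-month-3 bias of -0.062 SD, against about -0.002 SD with baseline-by-visit terms. This rests on 88 runs, so it supports the size of the bias but not an error rate.

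**The case against.** The best reply is that the article neither says that the slope is common nor rules out a baseline-by-time term, and that such detail often sits in a statistical analysis plan, which is not shown. This stands in part: an unseen plan may already contain the term. But the article lists the components of its primary model and names an interaction where it wants one, so an analyst following it as written would fit a single slope. The point concerns a stated model.

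Several limits stand in full. Neither a fading slope nor any size of imbalance is in the document. Clusters are assigned to arms within each site and site is in the model, so differences between sites need not feed the imbalance. With one follow-up, as for KAP, the issue cannot arise. The formula is exact only for a linear model with complete data; with a non-linear link it is a guide.

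A reader might go further and infer that the trial's main arm comparison, or its 12-month result, is seriously biased. The documents do not support that. The article plans pairwise arm comparisons without tying them to a visit; averaged over visits, the bias is zero. At month 12 alone, a separate simulation with falls in slope of 0.10 to 0.30 put null rejection at about 5-7% for a 0.2 SD imbalance and 6-10% for 0.3 SD, judged against the true standard error and before the planned Holm-Bonferroni adjustment. The high rates belong to the arm-by-time test under strong fading, and the article does not say how it will use that test.

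**Conclusion.** The point holds as a conditional, minor one. A single baseline slope next to an arm-by-time interaction leaves the arm-by-time terms open to baseline imbalance, in a design where imbalance is a real prospect. Two conditions are needed together: arms that differ at baseline, and a baseline slope that changes over follow-up. If either is absent, nothing is lost. If both are present, the damage falls mainly on the arm-by-time test and on statements about whether an effect lasts, and hardly on the size of the effect at any one visit. The same section also mentions ANCOVA; run separately at each visit, it would not have this problem, but the mixed model is the one named as primary.

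**What to change.** In the Data Analysis Plan, for outcomes with more than one follow-up, list the fixed effects as arm, visit (as a category), arm-by-visit, site, baseline value and baseline-by-visit. State that the arm-by-time test and any visit-specific contrasts come from this model.

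The cost is one sentence and, per outcome, three extra parameters with four follow-ups, one for laboratory outcomes on the Table 1 schedule, and none for KAP. With about 1,920 analysed participants (64 x 30) the loss of precision is negligible, and nothing is lost if the slopes prove constant. No new data, visits or participants are needed. If the statistical analysis plan already contains the term, only the article's wording needs to be aligned.

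### The baseline covariate cannot be counted on to control baseline imbalance between non-randomised clusters: a stable arm difference is only partly removed, and the rest looks like an intervention effect

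*Protocol article*

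**What the plan says.** Under Study Design and Setting, within each site "community clusters (wards/slum clusters) will be assigned to one of the 3 intervention arms". The reason given for working at cluster level is "to reduce contamination between participants and to align with local service delivery structures". Strengths and Potential Limitations concedes the consequence: "The nonrandomized allocation of participants may introduce selection bias, although cluster-based assignment and analytical adjustments will be employed to minimize its effects".

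The Data Analysis Plan describes the primary mixed model. It has "random intercepts for the clusters of communities and the individual study participants". Its fixed part reads: "Intervention arm, time, and their interaction will be modelled as fixed effects, with study site included as a fixed effect". For differences in the outcome at baseline it says: "To control the baseline imbalance in outcome variable values, the baseline value will be used as a covariate in the analysis". Then "Pairwise comparisons among the 3 study arms will be conducted", with Holm-Bonferroni adjustment and "statistical significance assessed at 2-tailed α level of .05". The only sensitivity analysis it names is multiple imputation, which addresses missing data.

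**The concern.** In a randomised trial, adjusting for baseline is unbiased and efficient, because any baseline difference is chance. Here it may not be. Suppose the clusters of one arm have a persistently better level of the outcome. A single baseline reading contains the persistent part plus visit-to-visit error. Conditioning on it compares people with the same observed score as though all arms regressed to one common mean, when each arm regresses to its own. Part of the old difference is then left in the arm contrast.

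No other part of the stated model removes it. Site terms do not, because every arm is present in every site. The cluster random intercept absorbs chance variation between clusters, not a systematic shift of one arm. Holm-Bonferroni deals with multiplicity. A larger sample shrinks the standard error and leaves the bias unchanged. An arm that starts better could look effective, and an arm that starts worse could have a real benefit hidden.

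**Working it through.** **Inputs from the protocol** (Data Collection and Sampling Strategy, sample-size paragraph): 64 clusters (16 per site), about 30 participants per cluster, ICC 0.02, attrition 15% to 20%, two-sided .05.

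**The plan's own figures.** Design effect = 1 + (30 - 1) x 0.02 = 1.58, as stated. 64 x 30 = 1920, and 1920 / 0.80 = 2400, as stated. So 30 per cluster is taken as the number completing.

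**Assumptions, because the protocol gives no value.** Delta is the stable arm difference in SD units, and rho is as defined by the correlation of baseline with follow-up within arms. Total within-arm variance is 1. There is no intervention effect, one pair of arms has 21 and 22 clusters, and the t test has 58 df.

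**Closed form, rho = 0.5, one follow-up visit.**
- Slope on baseline: (0.50 - 0.02) / (1 - 0.02) = 0.490.
- Bias at Delta = 0.1: (1 - 0.490) x 0.1 = 0.051 SD, close to (1 - rho) x Delta = 0.05.
- Residual variance of a cluster mean: (1 - 0.490)² x 0.02 + (0.98 - 0.48² / 0.98) / 30 = 0.0052 + 0.0248 = 0.0300.
- SE of the contrast: sqrt(0.0300 x (1/21 + 1/22)) = 0.053.
- Rejection at .05 with a shift of 0.051 / 0.053 standard errors: about 16%.

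The same formula at Delta = 0.1 gives 21% for rho 0.3, 11% for rho 0.7 and 8% for rho 0.85.

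**Simulation of the covariate model, single visit, rejection under no effect** (1000 runs per cell for rho 0.3, 600 for the others):

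| rho | Delta 0.1 | Delta 0.2 | Delta 0.3 |
|---|---|---|---|
| 0.3 | 19% | 62% | 92% |
| 0.5 | 16% | 48% | 79% |
| 0.7 | 11% | 27% | 55% |
| 0.85 | 6% | 14% | 29% |

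Averaging the four follow-up visits raises the Delta = 0.1 figures to 23%, 14% and 8% for rho 0.5, 0.7 and 0.85. With Delta = 0 the covariate model rejects in 3.5% to 5.2% of runs.

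**Change from baseline on the same data.** The contrast is unbiased under a stable difference and rejects in 2% to 6%. Its simulated SE at rho 0.5 is 0.058 against 0.053 for one visit (9% wider) and 0.046 against 0.040 for four visits (15% wider).

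**How large could Delta be?** At ICC 0.02 the between-cluster SD is sqrt(0.02) = 0.14. If 16 clusters per site were sorted perfectly by their true means, the top and bottom thirds would differ by about 0.30 SD and adjacent thirds by about 0.15 SD. The 0.3 column therefore needs near-perfect sorting, in the same direction at all four sites. The 0.2 column needs about two-thirds of that. The 0.1 column is the credible one, although 0.02 is itself only a planning value.

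**The case against.** The strongest reply is that the covariate model is one of two standard choices and no error in it has been shown. If the imbalance is chance, or if clusters were assigned on their observed baseline values, covariate adjustment is the unbiased analysis. In the second case the change contrast would be off by (1 - rho) x Delta in the other direction. This stands, and it is why the planned model should not be replaced.

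The model also contains an arm-by-time interaction, and the Abstract mentions pre-post comparisons. If T0 were an outcome row and the interaction against T0 were tested, a stable difference would cancel. The text neither says this nor excludes it. A baseline covariate with pairwise arm comparisons reads more naturally as a follow-up contrast, but the finding depends on that reading.

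A sensitivity analysis may also sit in a fuller document that is not shown, so its absence from the article is not the complaint. What the article does state is that the covariate controls the imbalance, and that does not hold for a stable difference. The limitations section admits selection bias but relies on analytical adjustments to reduce it, and for the outcome's own baseline this covariate is the stated adjustment.

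A reader might infer that the trial's false-positive rate will far exceed 5%, or that fitting arms to local service structures shows that they differ. The documents support neither. That phrase explains why allocation is by cluster, no passage reports a stable difference, and the highest rates come from imbalances that strain the stated ICC.

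**Conclusion.** The point holds conditionally. Non-random allocation permits a stable baseline difference between arms, and the stated remedy would remove only part of it. At 0.1 SD, the size that sits comfortably with an ICC of 0.02, the single-visit pairwise error rate is about 10% to 20% instead of 5% for rho 0.3 to 0.7, and barely raised (6% to 8%) at rho 0.85. The spurious effect itself is then about 0.03 to 0.07 SD, well below the planned 0.30. It would matter most for a modest declared difference. The result rests on three things the protocol does not settle: that a stable difference exists, the value of rho for each outcome, and that T0 is a covariate and not also an outcome row. A change to the plan is worthwhile because the guard is cheap, not because a large bias has been demonstrated.

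**What to change.** In the Data Analysis Plan:

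1. Replace the claim that the covariate controls baseline imbalance with a statement that it only partly corrects stable baseline differences between non-randomised arms.
2. For each primary outcome, prespecify one sensitivity analysis: T0 as an outcome row, arm-specific baseline means, no baseline covariate, and the same site term, random effects and Holm-Bonferroni correction. Test the arm-by-time difference in change from T0.
3. Report both estimates side by side. State that the covariate model is unbiased if imbalance is chance or allocation used observed baseline values, and that the change model is unbiased if imbalance is stable. Interpret disagreement as uncertainty due to non-random allocation.

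Do not require both models to be significant. With a true 0.30 SD effect in an arm that starts 0.3 SD worse, the covariate model at rho 0.3 has slope (0.30 - 0.02) / 0.98 = 0.286 and expects only 0.30 - (1 - 0.286) x 0.3 = 0.086 SD. Joint power is then about 27% (about 78% at rho 0.5), against 99% or more for the change contrast alone. Such a rule would bring back the masking that the second analysis is meant to reveal.

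The cost is a change of wording, one extra model on data already scheduled (Table 1 lists T0 for every tool), and a standard error up to about 15% wider for the change contrast. Precision can be spared: 1920 completers give about 99% power at d = 0.30.
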